### Outcomes

#### Transplant Knowledge

Our primary outcome measure is level of DDKT and LDKT knowledge. Patients will be asked 17 true/false and 8 multiple choice questions about the basic facts, advantages, risks and outcomes of DDKT and LDKT to assess knowledge levels (e.g., “Transplant recipients are at risk of developing high blood pressure and high cholesterol,” “The transplant team will let a living donor back out from donating on the day of the surgery”).

#### Informed Decision Making

Informed Decision-Making will be assessed in two ways. First, patients will be asked three questions: “I have all the facts I need to make an informed decision about whether to pursue DDKT/LKDT/remain on dialysis” (agree/disagree). Each of these questions will be treated as an individual item and analyzed separately. We also will administer the decisional conflict scale [49] to assess factors contributing to patients’ uncertainty in making health-related decisions, and patients’ assessment of their perceived effective decision-making.

#### Small Steps toward DDKT and LDKT

Several action steps toward pursuit of both DDKT and LDKT will be assessed using validated measures (e.g., “Do you plan to call the transplant center to begin evaluation,” “Do you plan to share your interest in living donation with your family and friends?”) [50, 51], each of which the patient will report as having “already done,” “planning to do,” or “don’t plan to do.”

#### Decisional Balance and Self-Efficacy

Validated Decisional Balance measures will assess patients’ perceived importance of the possible positive and negative outcomes of LDKT and DDKT. Patients will be given the prompt “How important is this statement to your decision about transplant?” and then be asked to respond to 24 positive and negative statements (e.g., “I would not have to be on dialysis,” “I would feel guilty having someone donate to me”). Patients will be prompted to respond on a 5-point Likert-type scale (1 = "Not important" through 5 = "Extremely important") [50, 51]. A Self-Efficacy scale measures how confident an individual is in their ability to pursue transplant if they encounter challenges along the way with 14 questions. Patients are asked, “How confident are you that you could get a transplant even if…,” followed by a potential challenge, “You didn’t have your own transportation to get to the transplant center?” Patients responses will range from (1) = " Not at all confident" to (5) = " Completely confident" [50, 51].

### Predictors and Covariates

#### Demographics Clinical and Cultural Factors

Demographic clinical, and cultural characteristics will be assessed including age, sex, race/ethnicity, whether or not a patient is on dialysis and what type (i.e., hemodialysis or peritoneal), and patient comorbidities (e.g., polycystic kidney disease). Additionally, a patient’s health-related quality of life will be measured with the use of the Health Related Quality of Life-4 (HRQOL-4) scale [52] and medical mistrust will be measured using the Medical Mistrust Index, a validated scale that assesses how much patients trust health care organizations (e.g., “When healthcare organizations make mistakes they usually cover it up”) [53, 54].

#### Socioeconomic Transplant Derailers

We will also assess potential SES derailers that may influence patients’ experience with transplant evaluation including level of education, employment status (full time, part time, disability, other financial assistance programs, no employment), and the quality of health insurance they have (private, government, multiple sources, no insurance). Additional SES derailers assessed include feelings of safety in their neighborhood, family obligations, income vulnerability [55], and access to transportation [56]. We will also measure patients' access to multiple technologies and resources, such as having a computer or cell phone, access to the internet, and a DVD player.

#### Prior Transplant Education

As one of the primary outcome measures is transplant knowledge, patients’ level of prior LDKT and DDKT education will also be evaluated. Patients will be asked a series of four Yes/No questions about their past behaviors (e.g., “Have you read brochures about transplants?”), and if a patient positively endorses a statement, they will be asked how many hours they have dedicated to each educational activity.

#### Health Literacy

Patients will respond to two items: “How often do you have someone (like a family member friend, hospital/clinic worker or caregiver) help you read hospital materials?” and “How confident are you filling out forms by yourself?” [57].

#### Evaluation and Process Measures

In the follow-up survey, patients will be asked about the helpfulness of the *ETH* resources. Patients will also be asked whether they agree with 7 statements relating to how helpful they viewed the materials provided to them (e.g., “The materials were easy to understand,” “The materials were overwhelming”) and the educator conversations (e.g., “The Explore Transplant Educator was helpful”, “The Explore Transplant Educator listened to what I had to say”).

### Data Management and Statistical Considerations

#### Data Management

To ensure participant confidentiality and privacy all data will be stored in university-maintained, secured servers. All study data will be captured in electronic databases within the Research Electronic Data Capture (REDCap) system [58]. Study personnel can check on patients’ records by examining their data entry form or through reports generated in REDCap. The records of patients who refuse to participate or are never successfully recruited into the study will be retained in the REDCap registration database and de-identified at the end of the study so that patterns in recruitment can be analyzed and reported.

#### Power and Sample Size

Power analyses were based on changes in transplant knowledge, our primary study outcome. The study design and analyses were treated as a test of the differences in mean knowledge score change between patients in the *ETH*-PG, *ETH*-EG, and Control conditions, 8–10 months post-baseline. Power calculations were based on the number of dialysis centers per condition, the number of individuals per dialysis center, the expected intra-class correlation, and the estimated variability of the outcome variable [59]. Based on the original *ET* trial [19], we estimated that a mean knowledge change score of 2.0 points would be needed to detect a significant difference between patients receiving standard-of-care, *ETH*-PG, and *ETH*-EG. It was assumed that patients coming from the same dialysis centers would have correlated knowledge scores. Since we are examining 3 conditions, a Bonferroni correction was required to adjust the Type 1 α for comparison of 3 group means (0.05/3 = 0.017). Based on these assumptions, we calculated that a design of 150 patients per condition, 450 patients total, will be required to find a mean change of 2.0 points in knowledge between groups at 90 % power. Expecting an approximately 20 % attrition rate over time, we are oversampling (180 patients per condition) to ensure that we have sufficient power to be able to assess our primary endpoint at the completion of the study period.

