### RCT Overview

This RCT has three conditions with equal allocation of patients to each condition: (1) the control condition or standard-of-care; (2) the *ETH* Patient-Guided (*ETH*-PG) condition; and (3) the *ETH* Educator-Guided (*ETH*-EG) condition (Fig. 2). All enrolled patients will complete a baseline survey and a follow-up survey, 8 to 10 months post-baseline. We will recruit 540 patients at the start of the 8 month educational intervention period to complete the baseline survey, with 180 patients in each condition. After attrition, 150 patients in each condition (*n* = 450 total) are expected to complete the follow-up survey.

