#### Statistical Analyses

Where feasible and appropriate, multiple imputation will be used to account for missing data [60]. Multilevel random effects models (MRMs) will also be used to account for correlated data (dialysis center clustering and serial measurement). We will compare the characteristics of patients who refuse to join the study or are never successfully contacted to those who do not, as well as patients who drop-out to those who do not, to determine if the patient selection procedure has biased the sample.

We will compare the difference in mean knowledge change, change in self-efficacy, and change in decisional balance (baseline to follow-up survey) of participants in the 3 study arms using MRMs with normal outcome distributions. A MRM with a normal outcome distribution will also be used to test for mean differences in the Decisional Conflict Scale at 8 months post-baseline, and Rao-Scott χ^2^ tests adjusting for dialysis center clustering will be performed to test for differences in patients’ answers to the informed decision-making items on the follow-up survey: “I have all the facts I need to make an informed decision about whether to stay on dialysis/pursue DDKT/pursue LDKT” (agree/disagree). Rao-Scott χ^2^ tests will also be used to test differences in the proportion of patients in each condition who took each small step toward transplant (e.g., “Do you plan to share your interest in living donation with your family and friends?”), operationalized as the number who had not taken each step at baseline but had at follow-up.

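### The Bonferroni level of 0.05/3 is valid, but with exactly three arms a prespecified Shaffer step-down gives the same error guarantee and never less power

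*Protocol article*

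**What the plan says.** RCT Overview: "This RCT has three conditions with equal allocation of patients to each condition". The conditions are control, patient-guided ETH and educator-guided ETH.

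Power and Sample Size treats the primary outcome as a test of "differences in mean knowledge score change between patients in the" three conditions. On multiplicity it says "Since we are examining 3 conditions, a Bonferroni correction was required to adjust the Type 1" error rate "for comparison of 3 group means (0.05/3 = 0.017"). It then gives the target difference, "we estimated that a mean knowledge change score of 2.0 points would be needed to detect a significant difference", and concludes that "a design of 150 patients per condition, 450 patients total, will be required" to find that difference "in knowledge between groups at 90 % power".

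Statistical Analyses compares the change scores "of participants in the 3 study arms using MRMs with normal outcome distributions". It does not repeat the 0.017.

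**The concern.** Three pairwise comparisons do need error control. Bonferroni gives it by charging each comparison a third of the 5%, whatever the other comparisons show. With three means this is more than the guarantee needs. The three equalities are logically linked: if one is false, at most one of the other two can be true. Once one difference has been established, only one false rejection remains possible, and it can be tested at the full 0.05.

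The trial wants several answers from the same three arms: whether each ETH version beats usual education, and whether the telephone educator adds anything. The unused error rate therefore costs power on contrasts that matter, most of all on power to establish more than one of them.

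**Working it through.** **Inputs from the article.** Three arms, equal allocation; 150 analysed per arm; difference 2.0 points; power 90%; level 0.05/3 = 0.01667, printed as 0.017.

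**Assumptions.** Two-sided tests (the article does not say). The standard deviation and intra-class correlation are named as inputs but not given, so 150 per arm cannot be reproduced forwards. I back-solved an effective standard deviation, with any clustering inflation absorbed in it:

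SD = 2.0 × √(150/2) / (z for 0.05/6 in each tail + z for 90% power) = 2.0 × 8.660 / (2.394 + 1.282) = 4.71.

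This returns 90% by construction, so it does not confirm the sample size. It fixes the signal-to-noise ratio at 2.0 / (4.71 × √(2/150)) = 3.676. The comparison of methods depends on that ratio and not on the standard deviation itself.

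**Ceiling.** A single 2-point contrast tested at 0.05 with no adjustment has power Φ(3.676 − 1.960) = 95.7%. No valid rule can beat this for one contrast, so the most there is to gain is about 6 points.

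**Rules compared.**
- Bonferroni: each contrast at 0.05/3.
- Shaffer: smallest p-value at 0.05/3; if rejected, the other two each at 0.05.
- Global gate: 2-df test of condition at 0.05; if significant, each contrast at 0.05.

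I simulated 1,000,000 trials per setting with independent normal arm means and known SD. Means are in the order control, patient-guided, educator-guided.

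| Means and quantity | Bonferroni | Shaffer | Global gate |
|---|---|---|---|
| 0, 0, 0: familywise error | 4.4% | 4.4% | 5.0% |
| 0, 2, 2: familywise error | 1.7% | 5.0% | 5.0% |
| 0, 2, 2: power, each 2-point contrast | 90.0% | 94.2% | 94.9% |
| 0, 2, 2: power, both 2-point contrasts | 83.3% | 91.7% | 92.3% |
| 0, 1, 2: power, the 2-point contrast | 90.0% | 90.8% | 91.6% |
| 0, 1, 2: power, each 1-point contrast | 29% | 44% | 45% |
| 0, 2, 4: power, all three contrasts | 80.1% | 91.4% | 91.4% |

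The setting 0, 0, 2 agrees with 0, 2, 2 to within simulation error. With no adjustment at all, the familywise error at 0, 0, 0 is about 12%, so some correction is needed.

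**Are any Bonferroni rejections lost?** Under Shaffer none can be. Any p-value below 0.05/3 means that the smallest is too, so the first step passes, and the contrast then also meets 0.05. The simulation found none. Under the global gate, a Bonferroni rejection is lost in about 0.06% (0, 2, 2) to 0.26% (0, 1, 2) of trials, because the 2-df test can just fail when one pair just passes.

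**The case against.** **The plan is valid as it stands.** This is correct. Bonferroni controls the familywise error, 0.05/3 is the right division for three pairwise tests, and the 90% target is set after the correction. The plan claims no power that it lacks. A reader might infer that the article contains a statistical error here, or that 150 per arm is wrong. Neither follows. The statement that a correction was required is fair in substance, since unadjusted testing would run at about 12%; only the choice of this particular correction is open.

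**The gain depends on the third arm.** This is also correct. A patient-guided result midway between the other two is plausible, and there the planned 2-point contrast gains less than 1 point under Shaffer, with no gain at all in the chance of finding at least one difference. The larger figures concern joint success on several contrasts, which is not the article's stated 90% target. The 1-point contrasts gain most, but remain poorly powered at 44%, and the plan does not aim at 1 point.

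**It is not free.** Bonferroni has simple matching simultaneous intervals; the step-down and gated rules do not. The gated rule also needs a valid joint test under the multilevel model and, where used, multiple imputation, and makes every pairwise claim conditional on that test.

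**The analysis section names no decision rule.** A reader might count this as a defect. It is ordinary content of an analysis plan, which is not shown, and a journal article condenses. The point rests only on the correction that Power and Sample Size does state.

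**Conclusion.** This is a cheap improvement and not an error. With three arms, Shaffer's step-down uniformly dominates Bonferroni: the same 5% familywise guarantee, no rejection lost, and some gained. Power per true 2-point contrast rises by about 4 points (90% to about 94%), and for both by about 8 points (83% to about 92%), when the third arm equals one of the pair. It rises by only about 1 point (90.0% to 90.8%) on the 2-point contrast when the patient-guided arm lies midway, where the two 1-point contrasts go from 29% to 44%.

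These sizes assume two-sided tests, a standard deviation back-solved from the plan's own power statement, and approximately normal estimates with equal precision in each arm. A claim of clearly more power at no cost would go too far, given the dependence on the third arm and the loss of simple simultaneous intervals. The protection covers the three contrasts on the primary knowledge outcome only, not the secondary outcomes or the subgroup interactions.

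**What to change.** Before outcome data are seen, prespecify for the primary outcome: the three pairwise contrasts in mean knowledge change are estimated from the multilevel model; the smallest p-value is tested at 0.05/3; if it is rejected, the other two are each tested at 0.05. State the power under this rule, with the standard deviation and intra-class correlation used.

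A 2-df global test of condition at 0.05, followed by pairwise tests at 0.05, is an acceptable alternative where a valid joint test is available under the multilevel model and multiple imputation. It is slightly more powerful on average, but can lose an occasional Bonferroni rejection.

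Report Bonferroni simultaneous intervals beside the ordinary 95% intervals, and say that the step-down decisions need not match them exactly.

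The cost is one sentence on the rule and one on the intervals. Recruitment, data collection and the 150 per arm stay as they are.

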## Background

In the United States there are approximately 637,000 patients with end-stage renal disease (ESRD) or kidney failure [1]. There are two options for ESRD patients to sustain life: dialysis or a kidney transplant from a deceased or living donor [1–4]. Kidney transplantation, especially living donor kidney transplant (LDKT), offers ESRD patients 6 to 16 additional years of life and improved quality-of-life compared to remaining on dialysis [1–3]. However, the majority of ESRD patients–450,000 as of 2013– still remain on dialysis. Although dialysis is life-saving, it only replaces 10-15 % of normal kidney function and can lead to cardiovascular disease, infection, and other complications [5, 6]. Additionally, the chance of a dialysis patient being alive after 5 years without a transplant is only 40 % [7]. Acknowledging its benefits over dialysis, the Centers for Medicare and Medicaid Services (CMS) has required that all dialysis patients receive transplant education and be informed of their option for transplant within 45 days of initiating dialysis.

In general ESRD patients who are Black and of lower socioeconomic status (SES) are significantly less likely to receive transplant education, pursue transplant evaluation, and receive deceased donor kidney transplants (DDKTs) and LDKTs [8, 9]. In fact, patients with kidney disease from low-SES neighborhoods experience higher mortality rates [10]. These patients may be more likely to have particular concerns about the costs of transplant medication [11], loss of disability benefits if they should receive a transplant [12], and limited access to adequate transportation to transplant appointments [13, 14]. Many low-SES patients may receive treatment at dialysis facilities with systemic barriers, including limited staff availability to provide education about transplant [15–17] or limited access to transplant education materials [18]. Without information about the risks and benefits of DDKT and LDKT, dialysis patients who do not present at a transplant center are often unable to make informed decisions about how best to treat their kidney disease [19, 20].

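### The attrition allowance does not add up: 180 per condition less about 20% leaves 144 completers, not the planned 150 (a minor correction, costing about one point of power)

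*Protocol article*

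**What the plan says.** Two sections of the protocol article bear on this.

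- **Power and Sample Size.** The authors write: "we calculated that a design of 150 patients per condition, 450 patients total, will be required", in order to "find a mean change of 2.0 points in knowledge between groups at 90 % power". The significance level is Bonferroni-adjusted for three comparisons (0.05/3 = 0.017). The next sentence puts the loss at about 20% and gives the allowance for it: "attrition rate over time, we are oversampling (180 patients per condition) to ensure that we have sufficient power".
- **RCT Overview.** Recruitment is 540 patients, 180 in each condition. The section continues: "After attrition, 150 patients in each condition", 450 in all, are expected to complete the follow-up survey.

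So 150 per condition is the number needed at follow-up, 180 is the number enrolled, and the loss between them is put at about 20%.

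**The concern.** The three figures (180 enrolled, about 20% lost, 150 retained) cannot all hold. Losing 20% of 180 leaves fewer than 150, and keeping 150 of 180 means losing less than 20%. The two sections therefore imply different attrition rates for the same trial.

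At stake is whether the printed sample size delivers the printed power for the primary outcome. Enrolment, expected completers and power are figures that readers will take at face value, and at the planned attrition the completer count and the power are both slightly overstated.

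**Working it through.** **Inputs, all from the protocol article**

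- Needed at follow-up: 150 per condition, 450 in total (Power and Sample Size; repeated as expected completers in RCT Overview).
- Enrolled: 180 per condition, 540 in total (both sections).
- Attrition: about 20% (Power and Sample Size).
- Target: difference of 2.0 points, 90% power, α = 0.05/3 (Power and Sample Size). Sidedness is not stated; two-sided is assumed.
- Standard deviation, intra-class correlation, centers per condition and patients per center: named as inputs to the calculation, but no values given.

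**Step 1. Reproduce the 180.** Enrolment that leaves n after a proportion d is lost is n / (1 − d):

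150 / (1 − 0.20) = 187.5, so 188 per condition and 3 × 188 = 564 in total.

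This does not give 180. Multiplying up instead does: 150 × (1 + 0.20) = 180. The match is exact, but the article shows no formula, so this is the likely origin and not a documented one.

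**Step 2. Run the plan forward.**

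180 × 0.80 = 144 per condition; 3 × 144 = 432 in total.

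The shortfall is 150 − 144 = 6 per condition (6/150 = 4%) and 450 − 432 = 18 overall.

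**Step 3. Find the attrition that fits 180 and 150.**

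1 − 150/180 = 16.7%. Any higher rate leaves fewer than 150; for example, 18% leaves 147.6 and 19% leaves 145.8.

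**Step 4. Size the effect on power.** The article's 90% cannot be reproduced from first principles because the variance and clustering inputs are not printed. Instead, assume that 150 per condition gives exactly 90% and back-solve the effective standard deviation (normal approximation, two conditions compared, two-sided α = 0.05/3):

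SD = 2.0 / [(z₀.₉₉₁₆₇ + z₀.₉₀) × √(2/150)] = 2.0 / [(2.394 + 1.282) × 0.1155] = 4.71 points.

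At 144 per condition the standardised signal shrinks by √(144/150) = 0.980:

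(2.394 + 1.282) × 0.980 − 2.394 = 1.207, and Φ(1.207) = 88.6%.

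**Step 5. Vary the assumptions.**

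- One- or two-sided tests at α = 0.017 or 0.05, no clustering: 88.6% to 88.9%.
- Two-sided α = 0.05/3 with clustering, using the design effect 1 + (m − 1) × ICC, m patients per center, and losses spread evenly over a fixed number of centers: 88.6% to 89.5% for an assumed ICC of 0 to 0.2 and 20 to 50 centers per condition. The top of the range is ICC 0.2 with 20 centers. There m falls from 7.5 to 7.2 and the design effect from 2.30 to 2.24, so effective size falls only from 65.2 to 64.3 per condition.

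The loss against 90% is therefore about 0.5 to 1.4 percentage points.

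**The case against.** The best defence is that the rate is given only as approximate, that 16.7% might loosely be called about 20%, and that both sections agree on 150. This makes the slip easy to understand but does not remove it. The planning value lies above the 16.7% ceiling, so at the stated rate the design falls short of 150.

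A second defence is multiple imputation, which the Statistical Analyses section plans where feasible and appropriate. The power statement, however, rests on patients retained after attrition, and nothing in the article credits imputation with making good lost sample size.

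A third objection carries weight: the power figures above are not this design's own. They come from a back-solved standard deviation, and the authors worked with clustered inputs that are not printed. If 150 had been rounded up from a smaller requirement, power at 144 would be a little higher. This is why a range is given, and why a figure from this check should not simply be copied into the protocol.

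A reader might also infer that the attrition allowance is too small, since the Background section gives 40% five-year survival on dialysis without a transplant. The documents do not support that step. The figure is a general one, while this trial enrols patients aged 18 to 74 and excludes those already told they are not transplant candidates. Even under a constant hazard, deaths over 10 months would be 1 − 0.4^(10/60) = 14.2%, below both 16.7% and 20%. Nor does anything in the article point to attrition above 20%, so scenarios at higher rates would show no error in the plan.

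**Conclusion.** The inconsistency is real and follows from the printed figures alone: 20% attrition from 180 gives 144 per condition (432 in total), while 150 per condition (450 in total) requires attrition of no more than 16.7%.

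It is a minor correction. The shortfall is 6 patients per condition, and power at the stated attrition is roughly 88.6% to 89.5% instead of 90%. That range assumes that 150 gives exactly 90% and uses illustrative values for the clustering, because the article gives no standard deviation, intra-class correlation or cluster sizes.

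A reader might conclude that the trial is underpowered or that its sample size fails. The figures do not support this: a loss of about one point leaves power close to target, and the primary comparison is unaffected.

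**What to change.** Keep enrolment at 540 and bring the RCT Overview and Power and Sample Size sections into agreement in one of two ways:

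1. Keep 20% attrition. Replace 150 per condition (450 in total) as the expected completers with 144 per condition (432 in total), and restate power for 2.0 points at α = 0.017, recomputed from the authors' own clustered inputs. The result should be about 89%.
2. Keep 150 completers. State the attrition assumption as about 16.7% (one patient in six), if the authors consider that rate realistic.

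Either is a change of wording, with no effect on recruitment, conduct or analysis. The first makes the stated power slightly less favourable; the second leaves it at 90% but commits the authors to a lower loss rate. Raising enrolment to 188 per condition (564 in total, 24 more patients) would also restore consistency, but the small loss of power does not require it.
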